### Cost-effectiveness analysis

Detailed economic data will be collected throughout the trial to enable a comprehensive evaluation of the intervention's efficiency when compared to routine care. Data on HCU will be obtained from participants at times 1, 2 and 3 and data on all public hospital admissions will be obtained from Queensland Health. Standard costs will be applied to HCU in both arms (e.g. Australian-Revised Diagnostic Related Groups for hospital admission costs). The intervention arm will also incur the costs of the intervention including set-up costs that will be annuitized (e.g. computer, telephone line connections) and operating costs (e.g. TLC Coordinator).

Within-trial and modelled over the rest of life cost-utility analyses will be undertaken from the perspective of direct health care costs to the government. SF-36v2 scores will be converted to utility weights using the SF-6 D algorithm [32] for the calculation of quality-adjusted life years (QALYs) - the primary outcome for the economic evaluation. The incremental costs and QALYs will be calculated as the differences between participants in the intervention and routine care groups. The resulting incremental cost-utility ratio will provide a measure of the relative value for money of the intervention using the additional cost per QALY gained. One-way and probabilistic sensitivity analyses will be undertaken for all parameters with uncertainty and/or variability [33].

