## Methods/design

### Study design

The study is a two-arm prospective RCT in which a total of 340 adults with type 2 diabetes will be randomised to either the intervention (TLC Diabetes program) or 'routine care' control arm. Participants in both arms complete assessments at baseline (Time 1), 6-month follow-up (Time 2), and 12-month follow-up (Time 3).

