### Data analyses

Assessment of similarity of baseline characteristics across randomised groups will be performed using appropriate summary statistics. If any imbalances of characteristics between the two groups are identified, these will be adjusted for in the main analytical modelling as supplementary analyses. Evaluation of the TLC Diabetes intervention effect will be based on an intention-to-treat analysis. Analysis of covariance (with baseline score as the covariate) will be fitted to estimate differences by intervention group in changes over time at each time point. Analysis across all time points using all available data, including as much as possible those of participants lost to follow-up, will employ generalised estimating equations. Results will be expressed as estimated mean changes in primary and other outcome variables by group, and as overall mean excess intervention over routine care effects, all with corresponding 95% confidence intervals.

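### The rule for incremental QALYs and costs names no baseline adjustment, although baseline utility is collected and the clinical analysis adjusts for baseline

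*Protocol article*

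**What the plan says.** In the protocol article, the Cost-effectiveness analysis section makes QALYs the primary outcome of the economic evaluation and derives them from the quality-of-life instrument: "SF-36v2 scores will be converted to utility weights using the SF-6 D algorithm". The rule for the increments is: "The incremental costs and QALYs will be calculated as the differences between participants in the intervention and routine care groups". No estimator or covariate is named. On resource use the section says: "Data on HCU will be obtained from participants at times 1, 2 and 3". On uncertainty it says: "One-way and probabilistic sensitivity analyses will be undertaken for all parameters with uncertainty and/or variability".

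The Study design section places assessments at baseline, 6 and 12 months in both arms, and Table 1 lists the SF-36v2 among the measures taken at all three times. A baseline SF-6D utility will therefore exist for each participant who completes the instrument.

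The Data analyses section does name an estimator for the trial outcomes: "Analysis of covariance (with baseline score as the covariate) will be fitted to estimate differences by intervention group", applied to changes at each time point. If other baseline characteristics turn out to be imbalanced, "these will be adjusted for in the main analytical modelling as supplementary analyses". Neither provision is expressly extended to QALYs or costs.

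**The concern.** The same SF-36v2 data are used twice. As a clinical outcome they are compared with adjustment for baseline. Converted to utilities and accumulated into QALYs, they are described only as a difference between arms.

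The clinical provision does not carry over by itself. A QALY accumulates over the year, so it has no value at each time point and no baseline QALY that could serve as the baseline score. The covariate needed is baseline utility, and it has to be named.

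Baseline utility matters to a QALY in two ways. It is part of the area under the utility curve, and it predicts the later utilities. A chance baseline difference between arms therefore appears as a QALY gain or loss that the intervention did not cause. The QALY increment is the denominator of the cost-utility ratio, and cost-effectiveness is the second hypothesis and the secondary aim.

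**Working it through.** **Figures in the document.** The article gives no SD, effect or power for QALYs, costs or the ratio, so there is no stated figure to reproduce on this point. The only input taken from it is the number of completers: 340 × 0.70 = 238, which agrees with the Sample size calculations section.

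**Assumptions.**
- Equal allocation, so 238 / 2 = 119 per arm.
- QALY by the trapezoid rule over 0, 6 and 12 months: QALY = 0.25·u0 + 0.50·u6 + 0.25·u12.
- The same utility SD, s, at each visit, with a range of 0.08 to 0.15.
- The same correlation, ρ, between any two visits, with a range of 0.3 to 0.7.

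**Share of a baseline gap carried into the QALY increment.** This is the slope of QALY on u0: 0.25 + 0.50ρ + 0.25ρ = 0.25 + 0.75ρ.

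**Variance of the QALY.** s²·[0.25² + 0.50² + 0.25² + 2ρ(0.125 + 0.0625 + 0.125)] = s²·(0.375 + 0.625ρ).

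**Precision.** R² = (0.25 + 0.75ρ)² / (0.375 + 0.625ρ), and the ratio of adjusted to unadjusted standard error is √(1 − R²). The utility SD cancels from this ratio.

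| ρ | Slope | Var(QALY)/s² | R² | Adjusted SE / unadjusted SE | Inverse |
|---|---|---|---|---|---|
| 0.3 | 0.475 | 0.5625 | 0.401 | 0.774 | 1.29 |
| 0.5 | 0.625 | 0.6875 | 0.568 | 0.657 | 1.52 |
| 0.7 | 0.775 | 0.8125 | 0.739 | 0.511 | 1.96 |

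**Size of a chance shift.** The standard error of the baseline utility difference is s·√(2/119) = 0.1296·s. A one-standard-error imbalance moves the unadjusted increment by slope × 0.1296·s:
- lowest case (s = 0.08, ρ = 0.3): 0.475 × 0.0104 = 0.005 QALY;
- middle case (s = 0.10, ρ = 0.5): 0.625 × 0.0130 = 0.008 QALY;
- highest case (s = 0.15, ρ = 0.7): 0.775 × 0.0194 = 0.015 QALY.

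**Check by simulation.** In 4,000 simulated trials with s = 0.10, ρ = 0.5 and no true effect, the unadjusted difference had mean 0.000 and standard error 0.0107. The adjusted difference had mean 0.000 and standard error 0.0070. Both are unbiased over repeated randomisation, and the ratio 0.0070 / 0.0107 = 0.65 agrees with the formula.

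**Costs.** The article gives no cost SD and no correlation between baseline and follow-up cost, so no corresponding figure can be derived.

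**The case against.** The strongest reply is that the article is silent on adjustment and does not reject it. A difference between groups is the ordinary definition of an increment, and a regression-adjusted difference also satisfies it. The words raw and unadjusted do not appear. The document is a journal article with two paragraphs on economics, and a fuller economic plan may name the covariates. This stands against reading the article as a deliberate choice of raw differences. It does not remove the point: the article gives a calculation rule for its primary economic outcome, and that rule, followed literally, yields an unadjusted difference. Read generously, it leaves the choice open until baseline data have been seen.

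A reader might infer three stronger things that the article does not support:
- **That the plain difference is biased.** Under randomisation it is not. The cost is lost precision, and a shift in any trial that happens to be imbalanced.
- **That baseline health-care use is collected and then ignored.** Table 1 lists utilisation and admissions as secondary outcomes, so the baseline-adjusted clinical analysis may well use them.
- **That imbalance will decide the sign of the ratio.** This depends on how small the true QALY gain is, and the article gives no figure for it.

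The planned sensitivity analyses are only a partial answer. As described, they vary uncertain parameters, and baseline adjustment is not among the analyses named. The provision for observed imbalances is supplementary, so even if it were extended to QALYs it would leave the main estimate unadjusted.

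Finally, the SD, the correlation and the trapezoid weights are all assumptions. That is fair, but the precision ratio does not depend on the SD, and even at a correlation of 0.3 the standard error falls by 23% with adjustment (1 − 0.774 = 0.226).

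**Conclusion.** The point holds as a gap in a stated rule. The article defines incremental QALYs and costs without baseline adjustment, although it collects baseline utility and adjusts for baseline in the clinical analysis. Over the assumed range of correlations, the loss of precision in the QALY increment is too large to leave to chance wording. For scale, at ρ = 0.5 adjustment is worth 1 / (1 − 0.568) = 2.3 times the sample size for this comparison.

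The results rest on equal allocation with 119 completers per arm, the trapezoid weights, and equal SDs and correlations across visits. For costs the point is one of consistency only, because no gain can be shown.

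**What to change.** Replace the sentence that defines the increments with wording to this effect: *Within-trial incremental QALYs will be estimated by regression on arm, adjusting for baseline SF-6D utility. Incremental costs will be estimated by regression on arm, adjusting for cost in the baseline period where the Time 1 look-back period allows.*

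The joint model for costs and QALYs and the method for intervals can be left to the economic analysis plan. The statement should be fixed before outcome data are compared by arm, so that adjustment does not depend on the imbalance observed.

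For QALYs the change costs only wording, since the SF-36v2 is already collected at Time 1. For costs the article does not state the look-back period of the Time 1 utilisation questionnaire. The sponsor should check that it gives a usable baseline cost before committing to that covariate.

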## Discussion

Previous trials of automated TLC systems targeting physical activity, nutrition and medication adherence have demonstrated the effectiveness of such technology to improve health behaviours and chronic disease self-management [13,16,17]. To date, this innovative and accessible form of self-management support program has not been formally tested in relation to diabetes management and its cost-effectiveness has not been examined. Therefore, this study will provide valuable information on the effectiveness, user-acceptability and feasibility of this telehealth system. It addresses the need to investigate new approaches to deliver ongoing and regular diabetes self-management support to relieve health systems from the growing demands caused by the increasing prevalence of diabetes around the world.
